## Abstract

**Background:**

Regular exercise is an effective method for reducing pain and disability in patients with knee osteoarthritis (OA), as well as improving body composition. Thus, a combination of both resistance and aerobic training (circuit training) has shown to be promising for this population. However, access to physical therapy is limited by physical distance, social isolation, and/or treatment costs. Remote rehabilitation seems to be an effective way to minimize these barriers, but the benefits are dependent on the participants’ adherence to the interventions provided at a distance. The objectives of this protocol are to compare the effects of a periodized circuit training applied via telerehabilitation with the same protocol applied in the face-to-face model for individuals with knee OA.

**Methods:**

This study presents a single-blinded protocol for a non-inferiority randomized controlled trial. One hundred participants diagnosed with knee OA (grades II and III Kellgren and Lawrence system), aged 40 years or more, and BMI < 30 kg/m^2^ will be randomly divided into two groups: telerehabilitation (TR) and face-to-face (FtF) circuit training. The FtF group will perform a 14-week periodized circuit training protocol supervised by a physical therapist, 3 times a week. The TR group will perform the same exercise protocol at home, at least 3 times a week. In addition, the TR group will be able to follow the execution and orientations of the exercises by DVD, a website, and online file sharing tools, and they will receive periodic phone calls in order to motivate, clarify, and inform some aspects of knee OA. The primary outcomes are changes in self-reported pain intensity (visual analog scale (VAS)) and physical function (Western Ontario and McMaster Universities Osteoarthritis Index (WOMAC)), with a primary end-point of 14 weeks and a secondary end-point of 26 weeks. Secondary outcomes include changes in other clinical outcomes, in morphological characteristics, adherence, acceptability, and treatment perspective.

**Discussion:**

A circuit training through telerehabilitation may contribute to developing early intervention in the causative and potentiating factors of the knee OA, verifying the effects of a low-cost, non-pharmacological and non-invasive treatment.

**Trial registration:**

Brazilian Registry of Clinical Trials (ReBEC) ID: RBR-662hn2. Registered on 31 March 2019. Link: http://www.ensaiosclinicos.gov.br; Universal Trial Number (UTN) of World Health Organization: U1111-1230-9517.

**Supplementary Information:**

The online version contains supplementary material available at 10.1186/s13063-021-05856-8.

## Administrative information

Note: the numbers in curly brackets in this protocol refer to SPIRIT checklist item number. The order of the items has been modified to group similar items (see http://www.equator-network.org/reporting-guidelines/spirit-2013-statement-defining-standard-protocol-items-for-clinical-trials/).

## Introduction

### Background and rationale {6a}

The knee joint is one of the most affected, leading to several functional, social, and economic consequences [1].

Obesity is one of the risk factors for OA. Muscle tissue is widely affected by fat accumulation, undergoing functional changes due to changes in the orientation of muscle fibers, thus decreasing the capacity to produce strength and physical function [1, 2]. A recent systematic review found that knee OA appears to lead to a higher amount of infiltrated fat in the thigh muscles when compared to people without knee OA regardless the body mass index (BMI) [3].

Among the therapeutic programs for patients with knee OA, physical exercise has shown to be promising in relieving pain and improving physical function [4]. Exercise protocols used to treat knee OA patients focus on improving aerobic capacity, quadriceps strength, and lower limb performance [5]. Therefore, a combination of both resistance and aerobic training has shown promising results for this population [6].

Circuit training (CRT) consists of a repetitive sequence of calisthenic exercises with shorter rest periods, which keeps the heart rate elevated throughout the training session [7]. This exercise model allows gain in muscle mass, improved body composition and functional capacity, and gain in muscle strength and cardiovascular benefits [8, 9].

Considering the benefits of CRT, our research group has been investigating the effects of a periodized circuit training protocol on non-obese individuals with knee OA, in different parameters, including inter and intramuscular fat [7]. Thus, a recent randomized controlled trial was conducted with this population, subjected to three different protocols: circuit training (CRT), strength training, and educational protocol [10]. The results showed that, in addition to the benefits of decreasing self-reported symptoms and physical function in the exercised groups, only the CRT group had a greater improvement in body composition measures, especially in thigh intermuscular adipose tissue. Thus, given that this exercise modality can bring significant benefits to individuals with knee OA, the disclosure of this therapy and patient adherence need to be tested.

Although the benefits of exercise are widely described, most people with knee OA do not meet the physical activity guidelines for good health [11], which are specific physical activity levels, such as frequency, intensity, and duration necessary for this purpose [12, 13]. Therefore, promoting continuous adherence is fundamental and a challenge for all involved professionals [14]. Physical therapists are often responsible for prescribing physical exercises for patients with knee OA. Physical therapy sessions are traditionally a face-to-face consultation, but for many people access to physical therapy is limited by physical distance, social isolation, and/or inability to afford the costs [15].

Telerehabilitation has been used adopting telecommunications technology as a service provider. Studies have shown that this treatment method provides improvements in physical activity and pain levels for people with chronic knee pain [16]. Additionally, face-to-face interventions, as well as those performed at distance, conducted electronically, resulted in similar clinical improvements after 12 weeks of treatment in patients with knee and hip OA [17]. Thus, telephone service models offer great potential to increase access to physical therapists and align with contemporary care models [18].

The implementation of any telerehabilitation method depends on the accessibility and familiarity of those receiving the intervention [19]. This means that the results of telerehabilitation can be influenced by geography (e.g., country) and socioeconomic status, both influencing the access and availability of the technologies needed for telerehabilitation. Countries such as the USA, Norway, Japan, and Australia are among the top 25 countries (out of 139 countries) in the Networked Readiness Index (NRI) [20]. Developing countries are ranked in the bottom half of the list of countries, with a considerable difference in NRI compared to the top countries [20]. To date, no study has evaluated the effectiveness of a telephone-type circuit training protocol in individuals with knee OA, specially conducted in a developing country.

Thus, it is essential that tools such as telerehabilitation be used to facilitate access, disseminate specific treatments, and increase adherence to physical exercise in this population. Therefore, comparing the effects of a face-to-face and telerehabilitation periodized circuit training protocol on the clinical characteristics of patients with knee OA seems relevant to clinical practice, as it may produce applicable results that are easily accessible to the health service. In addition, since the concentration of adipose tissue in the muscle has been described as a risk factor for the development and progression of knee OA, it is important to investigate the muscle morphological changes of patients with knee OA and its resulting clinical alterations.

## Objectives {7}

The primary aim of this randomized controlled trial is to determine if the periodized circuit training applied via telerehabilitation is just as effective to the same training applied face-to-face for improving pain intensity and physical function at 14 weeks (primary time-point) and 26 weeks (secondary time-point), in individuals with knee OA.

Secondary aims are to compare clinical (muscle strength and pain catastrophizing) and morphological characteristics (body composition, intermuscular adipose tissue, and muscle architecture), as well effectiveness, adherence, acceptability, and treatment perspectives 14 and 26 weeks after treatment. Safety endpoint will be determined by recording the number of adverse events during the intervention period.

## Trial design {8}

The present protocol is a non-inferiority randomized, parallel, single-blind trial with 1:1 allocation to the involved groups studied. This study was prospectively registered in the Brazilian Registry of Clinical Trials (ReBEC) under identifier RBR-662hn2 and with Universal Trial Number U1111-1230-9517. The following methodology is in full agreement with the OARSI (Osteoarthritis Research Society International) recommendations for randomized controlled trials (RCTs) [21], the Consolidated Standard of Reporting Trials (CONSORT) [22], and the SPIRIT (Standard Protocol Items for Randomized Trials) [23].

## Methods: participants, interventions, and outcomes

### Study setting {9}

Participants from the community of São Carlos, Brazil, will be invited to participate in this study. Participants will be recruited by ads in local newspapers, magazines, and social media. After declaring interest, participants will be phone interviewed by the Trial Coordinator to verify if they meet the primary eligibility criteria. If they were deemed eligible, a face-to-face evaluation will be scheduled to confirm the definitive eligibility criteria.

### Eligibility criteria {10}

#### Primary inclusion criteria (phone screening)

Participants must meet the following criteria to be eligible for the study:
i.Aged ≥ 40 years [24]ii.Report knee joint painiii.Report history of knee pain ≥3 months

#### Primary exclusion criteria (phone screening)

Participants will be excluded during the phone screening if they:
i.Report body mass index (BMI) ≥ 30 kg/m^2^ [10, 25]ii.Are currently consulting a physical therapist, walking more than 30 min continuously daily, or doing regular physical exercises (more than twice a week) up to 6 months prior to the beginning of this study [7]iii.Have had previous knee surgery [7]iv.Have used corticosteroid infiltration in the knees up to 6 months prior to this study [26]v.Have a history of lower limb trauma within 30 days prior to evaluation [26]vi.Have used chondroprotectors [26]vii.Have rheumatic diseases [7]viii.Have uncontrolled heart disease [26]ix.Have history of severe muscle damage (above grade I) [7]x.Have motor deficit due to neuromuscular disease [7]xi.Have any medical restriction that precludes participation in this study [26]

Definitive eligibility will be screening during the first face-to-face evaluation based on the criteria below.

#### Definitive inclusion criteria (face-to-face evaluation)

Participants must meet the following criteria to be eligible for the study randomization:
i.Report an average pain score ≥ 400 mm on analog visual scale [10]ii.Report at least one of the following: age > 50 years, morning knee stiffness ≤30 min, and crepitus [27]iii.Radiographically diagnosed with unilateral or bilateral knee OA grade II or III according to the criteria of Kellgren and Lawrence (1957) [28]

For participants with bilateral OA, the most symptomatic side will be considered for evaluation.

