#### Pain Intensity

Pain intensity will be measured using Visual Analog Scale (VAS). This is a reliable measure of pain [35] consisting of a 100-mm line in which participants must mark between the left side (0, representing “no pain”) and 100 (representing “the worst pain imaginable”). This measure will be self-reported on a paper form.

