### Sample size {14}

Sample size was based on detecting non-inferiority of telerehabilitation circuit training in comparison to the face-to-face method at 14 weeks after randomization, considering the primary outcomes pain (VAS) and disability (WOMAC function sub-scale). For change in VAS, a non-inferiority margin (NIM) of 16 mm was chosen as this is less than the minimum clinically important difference (MCID) of 17.5 mm from a 100-mm VAS for OA patients [55]. For change in WOMAC function sub-scale, a NIM of 7.5 units (11% of scored 0–68) was chosen as this is less than the MCID of 12% (8.16) of improvement from baseline in OA research [56]. Assuming standard deviations (SD) for changes from baseline of 17.9 mm and 12.12 units for pain intensity and physical function respectively [10, 25], 80% power and a one-sided 2.5% significance level, we needed 20 people per arm for change in pain intensity and 41 people per arm for change in physical function. However, considering 18% loss to follow-up, we needed 25 and 50 people per arm for change in pain intensity and physical function, respectively. Thus, a total of 100 people will be included in the trial. No adjustments for multiplicity was made. Sample size calculation was performed using the software G*Power, version 3.1.

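### The pain threshold for entry is 400 mm on a scale that ends at 100 mm, and the article does not let the reader recover the intended value

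*Protocol article*

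**What the plan says.** The section on definitive inclusion criteria opens with a mandatory condition: "Participants must meet the following criteria to be eligible for the study randomization". The first item in that list is "Report an average pain score ≥ 400 mm on analog visual scale". The section Implementation {16c} then randomises everyone who consents and fulfils the inclusion criteria, so the item decides who enters the trial.

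The section Pain Intensity defines the scale used for the primary pain outcome as "consisting of a 100-mm line in which participants must mark between the left side" (0, no pain) "and 100 (representing “the worst pain imaginable". Sample size {14} uses the same scale length when it justifies the pain margin against a "minimum clinically important difference (MCID) of 17.5 mm from a 100-mm VAS for OA patients".

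Trial status reports that the first two blocks of recruitment, allocation and analysis are finished, and that the final block of 40 had not started.

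**The concern.** An entry criterion has to be a value that the measuring instrument can return. Here a mandatory criterion, on the measure that is also a primary outcome, lies outside the range of the instrument.

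What is at stake is the description of the population. Pain at entry determines how much a VAS score can fall. A reader of a non-inferiority result for pain needs to know what minimum level of pain participants had when they started, and the article states a minimum that cannot be true. Because the last block was still to be recruited, the article also gives no usable value against which its screening could be checked.

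**Working it through.** **1. The threshold against the scale.**

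- Entry threshold: 400 mm or more (definitive inclusion criteria).
- Maximum score: 100 mm (Pain Intensity), with the same length given in Sample size {14}.
- Ratio: 400 / 100 = 4. No attainable score meets the criterion.

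**2. Is there a reading under which 400 mm is possible?**

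- *A sum of several VAS items.* At least 400 / 100 = 4 lines would be needed, each marked at its maximum. The article describes one line. The criterion also refers to an average, and an average of 0 to 100 scores cannot exceed 100.
- *A WOMAC score.* The article describes Likert scoring from 0 to 4 per question. The function subscale has 17 questions, so its maximum is 17 × 4 = 68, as stated. If the same scoring applied to all 24 questions, the maximum would be 24 × 4 = 96. Neither is in millimetres and neither reaches 400.
- *A second VAS used only for screening.* None is described.

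**3. Can the intended value be found elsewhere in the article?** The phone screen asks for knee pain and a history of at least 3 months, with no intensity. The abstract gives radiographic grade, age and BMI, with no pain level. The criterion cites an earlier trial by the same group, which is not available here. The answer is no.

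**4. Does the error reach the sample size?** The stated inputs are a pain margin ("a non-inferiority margin (NIM) of 16 mm was chosen"), a function margin ("a NIM of 7.5 units (11% of scored 0–68) was chosen"), standard deviations of change of "17.9 mm and 12.12 units for pain intensity and physical function respectively", 80% power, one-sided 2.5% and 18% loss. With a true difference of zero and the normal approximation,

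n per arm = 2 × (1.960 + 0.842)² × (SD / margin)², where 2 × (1.960 + 0.842)² ≈ 15.70.

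- Pain: 15.70 × (17.9 / 16)² = 15.70 × 1.252 = 19.6, so 20. With loss: 20 / 0.82 = 24.4, so 25.
- Function: 15.70 × (12.12 / 7.5)² = 15.70 × 2.611 = 41.0, so 41. With loss: 41 / 0.82 = 50.
- Total: 2 × 50 = 100.

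The plan's figures reproduce. A noncentral-t calculation gives 21 and 42 before loss, a difference of one per arm that has nothing to do with this point. The entry threshold appears nowhere in the formula, so the total is the same whatever the threshold is.

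**5. What was done in practice?** The planned stages are 20, 40 and 40. The first two, 20 + 40 = 60 by plan, are reported complete. People were therefore enrolled, and 400 mm cannot have been the rule applied to them. The figure of 60 rests on planned stage sizes; the article gives no enrolled count.

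**The case against.** The strongest reply is that this is a typing or unit error in a condensed article. A figure that cannot be applied literally is unlikely to mislead anyone at enrolment, and nothing in the analysis uses it. Most of that stands. A slip is the likeliest explanation, and the sample size, margins and decision rule are unaffected. It does not remove the point, because the figure sits in a mandatory criterion and the article offers no means of correcting it.

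Two further replies stand in part. The article does not say outright that the entry score is taken on the same VAS as the outcome; that is an inference, though no other VAS is described. The full or ethics-approved protocol may carry the right value, and the cited earlier trial may too. Neither can be seen here, so the accurate statement is that the threshold cannot be recovered from this article, not that none exists.

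A reader might also infer more than the documents support:

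- *That nobody is eligible.* This is true of the wording only. Two blocks were recruited.
- *That low baseline pain pushed both arms to the bottom of the scale and so favoured non-inferiority.* Someone starting below 16 mm indeed cannot improve by 16 mm, but that is a property of the scale. The article gives no baseline VAS data and nothing to suggest that such people were enrolled. Another threshold was evidently in use.
- *That the 16-mm margin or the 17.9-mm standard deviation loses its basis.* The margin is justified by a minimum important difference of 17.5 mm and the standard deviations by cited studies. Neither is derived from the entry threshold.

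**Conclusion.** The point holds as an internal inconsistency: the entry criterion is wrong as written. The threshold exceeds the maximum of the only VAS described by a factor of four, and the article contains no other value to put in its place. The consequence is confined to the description and verification of the trial population, whose minimum baseline pain is left unstated. There is no numerical effect on the sample size (20 and 41 per arm, 25 and 50 after loss, 100 in all) or on the margins, and no bias in the comparison is shown.

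The conclusion assumes that the entry score is taken on the VAS defined under Pain Intensity. That some other threshold was used in practice is inferred from the reported completion of the first two blocks.

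**What to change.** Reconcile the first definitive inclusion criterion with the scale defined under Pain Intensity. The sponsor should state, on the 0 to 100 mm scale, the threshold that was actually used at screening for the first two blocks, and confirm that it is the one in the ethics-approved protocol. The same value should apply to the final block of 40. If the entry score was taken on a different instrument from the outcome VAS, the article should name that instrument and give its range. This review does not propose a value, which must come from the trial's own records.

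The cost is one corrected figure, a look at the screening form used for the first two blocks, and a check against the approved protocol. The design, sample size and analysis do not change.

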#### Definitive exclusion criteria (face-to-face evaluation)

Participants will be excluded during the face-to-face evaluation if they:
i.Have cognitive impairment that compromise the understanding of the tests (obtained by Mini Mental State Examination (MMSE)) [29].

#### Screening definitive eligible criteria

##### Knee radiography

The presence of knee OA (K/L II and III) will be confirmed by radiographic examination. The exam will be performed bilaterally in the posteroanterior view with a 45° weight-bearing half-knee (orthostatic position), axial to the patellofemoral joint [30] and lateral, in the supine position at 45° of knee flexion. The images will be acquired and classified at the UFSCar University Hospital (UH) by an experienced radiologist.

##### Mini Mental State Examination (MMSE)

MMSE will be used as a screening test for cognitive loss, exclusion criteria of the present study. The MMSE consists of 11 items, divided into 2 sections. The first section requires verbal answers and questions for guidance, memory, and attention, and the second section is for reading and writing questions. The questions are performed in the order in which they are listed and can total a maximum score of 30. Thus, the following individuals will be considered to have cognitive impairment: illiterate with a total score of less than 20, individuals with 1 to 4 years of study with a total score less than 25, individuals with 5 to 8 years of study with a total score of less than 26.5, individuals with 9 to 11 years of study with a total score of less than 28, and individuals who studied for more than 11 years with a total score of less than 29 [31].

### Who will take informed consent? {26a}

All participants considered eligible by phone and face-to-face screening will receive oral and written information about the research procedures. The purpose, potential risks (e.g., muscular pain after doing exercise protocol and physical assessments), and possible benefits (e.g., improvement in daily activities and pain relief) involved in the study will be explained by the Trial Coordinator. After agreeing to participate, participants will sign an informed consent form. This study protocol has been approved by the Human Research Ethics Committee from the Federal University of São Carlos (CAAE: 05833118.6.0000.5504) and will be conducted according to the norms of National Health Council Resolution 466/2012 on research involving human beings.

### Additional consent provisions for collection and use of participant data and biological specimens {26b}

This randomized controlled trial will not use participant data and biological specimens from ancillary studies.

### Interventions

#### Explanation for the choice of comparators {6b}

According to the OARSI Clinical Trials Recommendations [21], usual care is a recommended comparator for interventions involving exercise. Thus, participants allocated to the control group will receive the face-to-face periodized circuit training protocol proposed by Almeida et al. [7] which has demonstrated improved physical function, muscle strength, and reduced intermuscular adipose tissue (IMAT) concentration in patients with knee OA [10].

